### Trial endpoints

NT-proBNP is used widely to monitor the therapeutic efficacy of agents for heart failure in clinical trials and is established as a prognostic biomarker for heart failure [21–23]. In addition, NT-proBNP-guided treatment for heart failure has been demonstrated to improve clinical outcomes in a randomized trial [24]. Therefore, the percent change in NT-proBNP levels from baseline to 24 weeks will be used as the primary endpoint in the CANDLE trial. The secondary endpoints are the values and changes in parameters after 24 weeks of treatment (or at discontinuation), including: (1) NT-proBNP, (2) glycemic control (HbA1c, fasting plasma glucose, plasma insulin, HOMA-R and HOMA-beta), (3) clinic systolic and diastolic BP and home BP (optional), (4) BW, (5) biochemical tests (lipid profiles and uric acid), (6) quality of life (MLHF scores) (7) echocardiographic cardiac function parameters (LVEF and E/e’) and severity and change in NYHA functional classification, and (8) renal function parameters (serum creatinine level, estimated glomerular filtration rate (eGFR), urinary albumin excretion, and urine L-FABP). Other secondary endpoints include clinical outcomes such as CV events, including all-cause death, non-fatal myocardial infarction, non-fatal stroke, hospitalization for heart failure, and changes in medications related to aggravation of heart failure. Safety endpoints include adverse effects and adverse drug reactions observed during treatment with the study drugs. The exploratory endpoints are changes in specific biomarkers after 24 weeks of treatment, including high-sensitivity troponin I, hsCRP, serum cystatin C, PTX3, RAGE, ANGPTL2, IL-8, and periostin. The findings of these biomarker assays may, in part, provide mechanistic insights on the effect of canagliflozin on CV pathogenesis.

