#### Analysis plan

The analyses of the primary and secondary endpoints will be performed in the FAS, which includes all patients who received at least one dose of treatment during the study period and did not have any serious violation of the study protocol, and had data collected after commencement of treatment. For the baseline characteristics, the summary statistics will comprise frequencies and proportions for categorical variables, and means and standard deviations for continuous variables. The patient characteristics will be compared using Chi square tests for categorical variables, and t tests for normally distributed continuous variables or Wilcoxon rank sum tests for continuous variables with a skewed distribution.

For the primary analysis comparing treatment effects, the least square mean and its 95 % confidence interval will be estimated using analysis of covariance (ANCOVA). To test for non-inferiority of the primary endpoint, the ANCOVA will be applied adjusted for age (<65, ≥65 year), HbA1c level (<6.5, ≥6.5 %), and left ventricular ejection fraction (LVEF; <40, ≥40 %). The secondary analysis will be performed in the same manner as the primary analysis.

All comparisons are planned and all *p* values will be two sided. *P* values <0.05 will be considered statistically significant. All statistical analyses will be performed using SAS software version 9.4 (SAS Institute, Cary, NC, USA). The statistical analysis plan will be developed by the principal investigator and a biostatistician before completion of patient recruitment and database lock.

Trial organization and oversight (details in Additional file 4).

Principal investigators of the CANDLE trial are [name] (Chief), Department of Cardiovascular Medicine, Saga University and [name], Department of Cardiology, Nagoya University Graduate School of Medicine. The Steering Committee will carry out planning, operating, analyzing, and presentation of the trial. The Executive Committee will supervise the trial design and operation of the study. The roles of DSMB and CEC are described in the section of Endpoint adjudication. The trial secretariat is in DOT INTERNATIONAL CO., LTD, Tokyo, Japan. Each of data management, monitoring, statistical analyses, and audit will be independently implemented on the basis of outsourcing agreement.

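### The single method stated for secondary endpoints, the primary's ANCOVA, does not suit the event outcomes or NYHA class, and leaves the continuous endpoints without their own baseline

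*Protocol article*

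**What the plan says.** All of this is in the protocol article.

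- **Analysis plan, primary method:** "the least square mean and its 95 % confidence interval will be estimated using analysis of covariance (ANCOVA". The covariates are in the next sentence: "To test for non-inferiority of the primary endpoint, the ANCOVA will be applied adjusted for age", followed by HbA1c and LVEF. All three are two-category versions of the minimisation factors.
- **Analysis plan, secondary rule:** "The secondary analysis will be performed in the same manner as the primary analysis". No other method for a secondary endpoint is named. The chi-square, t and Wilcoxon tests in that section are for patient characteristics.
- **Analysis plan, population:** "The analyses of the primary and secondary endpoints will be performed in the FAS".
- **Trial endpoints:** eight groups of parameters, taken as values and as changes. Group 7 includes severity of, and change in, NYHA class. Then: "Other secondary endpoints include clinical outcomes such as CV events, including all-cause death, non-fatal myocardial infarction, non-fatal stroke", continuing with heart-failure hospitalisation and changes in medication for worsening heart failure.
- **Measurements and Trial endpoints:** body weight, blood pressure, and blood and urine tests are taken at each visit. Echocardiography, the quality-of-life questionnaire and NT-proBNP are taken at baseline and at the final visit. Since changes are endpoints, baseline values must be available.

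**The concern.** This is a rule that is stated, not a detail left open. A later analysis plan that chose suitable methods for deaths or NYHA class would have to depart from the published sentence.

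The affected outcomes matter to this trial. Study overview and design frames the hypothesis as canagliflozin not worsening heart failure, and Endpoint adjudication sets up a blinded committee for clinical events. If the rule is followed as written, the adjudicated events get a model built for continuous measurements.

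For the continuous endpoints the issue is milder. Leaving out a baseline that the trial collects wastes precision and lets chance baseline differences into the week-24 comparison.

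**Working it through.** The plan gives no figure of its own on this point, so there is none to reproduce. The check is a count of endpoints by type, followed by what the stated model does with each type.

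**Step 1. Count from Trial endpoints** (lipid profile counted once, optional home blood pressure left out):

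| Type | Endpoints | Number |
|---|---|---|
| Continuous | NT-proBNP 1; glycaemic 5; clinic systolic and diastolic pressure 2; body weight 1; lipids 1; uric acid 1; quality of life 1; LVEF and E/e' 2; renal 4 | 18 |
| Ordinal | NYHA class | 1 |
| Event | death, myocardial infarction, stroke, heart-failure hospitalisation, heart-failure medication change | 5 |
| Total | 18 + 1 + 5 | 24 |

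So 6 of 24, one quarter, are not continuous.

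**Step 2. The stated model applied to events.** With the outcome coded 0/1, the difference in least-square means is an adjusted risk difference, which is an interpretable quantity. The difficulties are these:

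- The variance of a 0/1 outcome is p(1 − p), so it changes with risk, while ANCOVA assumes one common variance. With few events the normal approximation behind the confidence interval and p value is poor. The article gives no expected event rate, so how poor cannot be computed.
- Timing is ignored, and a patient lost early counts the same as one followed event-free for 24 weeks. Applying the planning dropout of 10 % to 125 per group gives 0.10 × 125 = 12.5 patients per group with possibly incomplete follow-up.
- An event has no baseline value, so a change from baseline has no counterpart.

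**Step 3. The stated model applied to NYHA class.** Patients enter in class I, II or III. A mean of class scores treats each one-class step as the same distance and normal errors as reasonable on a scale of three or four points. A mean can be computed, but it does not show how many patients improved or worsened.

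**Step 4. The stated model applied to the 18 continuous endpoints.** The covariates are age (<65, ≥65), HbA1c (<6.5, ≥6.5 %) and LVEF (<40, ≥40 %). Only HbA1c and LVEF therefore have any form of their own baseline in the model, and that is a two-level screening category. The other 18 − 2 = 16 have none.

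Let σ² be the variance at baseline and at week 24, and ρ the correlation between them, setting the three factors aside. The variance per patient is:

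- week-24 value alone: σ²
- change from baseline: 2σ²(1 − ρ)
- ANCOVA with own baseline: σ²(1 − ρ²)

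Relative to the last:

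- value alone: 1/(1 − ρ²), which is 1 at ρ = 0 and grows without limit as ρ approaches 1
- change: 2(1 − ρ)/(1 − ρ²) = 2/(1 + ρ), which is 2 at ρ = 0 and falls to 1 as ρ approaches 1

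The article gives no ρ, so only these ranges can be stated. For stable quantities such as body weight or eGFR, where ρ should be high, analysing the value alone loses most. The plan analyses both values and changes. Without own baseline, the two treatment estimates differ by the baseline difference between groups. With it, they are identical.

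**The case against.** **The sentence may not be meant for events.** It refers to the secondary analysis, not to every secondary endpoint. Trial endpoints separates parameters from other secondary endpoints, and the key secondary endpoints in the Abstract are all changes in parameters. This reading is fair. But the population sentence treats secondary endpoints as one class, and no second rule is given for events. Even on the narrow reading, NYHA class sits inside the parameter list and the missing own baseline is unaffected. Only the event part would shrink, to silence that an analysis plan can fill.

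**The article is condensed and an analysis plan is announced.** True, and the choice among Cox, log-rank, exact or proportional-odds methods belongs there. What stands is that the published sentence points to a different method.

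**A linear model is not meaningless here.** Correct. It yields a risk difference or a mean class score, so calling the estimates invalid would go too far. Unsuitable and potentially misleading is the right strength. Likewise, omitting baseline does not bias a randomised comparison on average.

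**Two stronger readings that a reader might infer are not supported:**

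- *That secondary endpoints are to be tested for non-inferiority and so lack margins.* The text ties non-inferiority to the primary endpoint ("To test for non-inferiority of the primary endpoint, the ANCOVA will be applied adjusted for age") and says that p "values will be two sided". An ordinary test of difference is at least as natural a reading.
- *That the rule "values <0.05 will be considered statistically significant", applied across the list, makes a false secondary benefit likely.* For 24 independent true nulls, 1 − 0.95^24 = 71 %. That counts significance in either direction. In favour of canagliflozin it is 1 − 0.975^24 = 46 %. Independence also fails for pairs such as creatinine and eGFR, or systolic and diastolic pressure. The Background cites earlier evidence of effects on weight and blood pressure, so all nulls being true is doubtful. The article names one primary endpoint, and handling of secondary multiplicity is commonly left to the analysis plan.

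**Conclusion.** The concern holds as a badly fixed analysis rule. Read as written, it assigns a linear model with least-square means to 6 of at least 24 secondary endpoints for which that model is unsuitable. It also leaves 16 of the 18 continuous endpoints with no adjustment for their own baseline and the other two with a two-level version only.

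This rests on the sentence covering the whole secondary list. If it was meant for the parameter list alone, the NYHA and baseline parts remain. The numerical effect on event results cannot be given because no event rate is stated. The loss of precision depends on correlations that are also not stated. The primary endpoint's analysis is outside this point, and no secondary margin or multiplicity adjustment is missing on this evidence.

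**What to change.** Replace the sentence on the secondary analysis with rules by endpoint type:

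- **Continuous endpoints:** ANCOVA on the week-24 value with the endpoint's own baseline plus the three minimisation factors, on the log scale for skewed measures (for example urinary albumin, L-FABP, insulin and the HOMA indices), reported as a two-sided estimate of difference with 95 % confidence interval.
- **CV events and heart-failure medication changes:** counts by group, with exact or time-to-first-event methods.
- **NYHA class:** an ordinal model, or a comparison of improved, unchanged and worse.

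A phrase calling secondary p values nominal would be useful but is optional.

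The cost is wording in the protocol and analysis plan, best settled before database lock. Patient numbers, visits and measurements do not change, provided event dates are recorded if time-to-event methods are chosen.

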## Discussion

The CANDLE trial is an ongoing, multicenter, prospective, randomized, investigator-initiated clinical trial that has the aim of testing the safety and non-inferiority of canagliflozin in T2DM patients with CHF. In this trial, eligible participants will be randomized to canagliflozin or glimepiride groups and receive the study drug in addition to their background medications for 24 weeks. The primary endpoint is the percentage change from baseline in NT-prBNP level after 24 weeks of treatment. This trial has the potential to generate novel evidence regarding the clinical relevancy of canagliflozin in T2DM patients with CHF.

Accumulating evidence suggests that T2DM has a major impact on the increased risk of micro- and macrovascular complications that are associated strongly with unfavorable clinical outcomes and poor prognosis [26–29]. Importantly, comprehensive medical intervention in diabetic management is encouraged at earlier stages of disease development in order to improve patient prognosis [30–32]. Although previous studies have shown that glucose-lowering therapy is important in the clinical setting, the beneficial effects on long-term outcomes and prognosis remain controversial [33–37]. For the management of diabetic patients, current guidelines state therapeutic goals for HbA1c levels, based on the patient’s background and tolerability to treatment [7]. In addition, for safety reasons it is essential that anti-diabetic agents do not increase the risk of CV events, and at least, are not inferior to conventional therapy [38]. Nevertheless, despite the increasing number of T2DM patients complicated with CHF, in whom a higher risk of CV events is possible, there is no clinical evidence on therapeutic goals based on safety and efficacy in this population. Therefore, establishment of therapeutic guidelines for T2DM patients with CHF is required.

Of the various conventional anti-diabetic agents, thiazolidine derivatives are effective for improving insulin resistance by enhancing insulin sensitivity in peripheral tissues, but need to be administered with caution because of possible adverse effects such as worsening of edema and heart failure [39, 40]. Dipeptidyl peptitadase-4 inhibitors have been shown to have neutral effects on CV outcome in both the EXAMINE (alogliptin vs. placebo) and TECOS (sitagliptin vs. placebo) trials [41, 42]. However, the SAVOR-TIMI53 trial (saxagliptin vs. placebo) demonstrated recently a significantly higher incidence of hospitalization for heart failure in the saxagliptin group, compared to placebo [43]. Therefore, at present the clinical use of anti-diabetic agents in T2DM patients with CHF is, in part, somewhat limited. As a consequence, although these patients are considered to be at higher CV risk and require more effective treatment strategies to improve their clinical outcome, no specific treatment guidelines have been established. Metformin is recognized widely as the first line strategy for treatment of type 2 diabetes in the USA and Europe, with some study showing a preference for metformin over sulfonylureas in diabetes patients with heart failure [44, 45]. However, metformin is not necessarily a first line treatment option in Japan [7]. Although the present study excludes patients with renal dysfunction who are prohibited to receive metformin, metformin is contraindicated in Japan for patients with heart failure because of the risk of lactic acidosis. In addition, it has been reported that decreased insulin secretion capacity has a pivotal role in the development of T2DM in Japanese subjects and accordingly sulfonylureas are used more frequently than metformin in Japan [46]. To our knowledge, there is no direct evidence showing that sulfonylureas increase the risk of heart failure. A phase III trial in the USA showed sulfonylureas had similar power to decrease HbA1c levels as canagliflozin 100 mg/day [14]. We therefore selected glimepiride as the comparison agent.

Previous clinical trials in T2DM patients demonstrated that SGLT2 inhibitors are well tolerated by patients and exert favorable effects on BP and systemic metabolisms such as body fat loss, in addition to improving glycemic control [10–12]. Experimental studies using animal models have shown that SGLT2 inhibitors also reduce inflammation and oxidative stress in hepatic, renal, and cardiac tissues [47–50], and therefore presumably would have a protective effect on the CV system. These class effects would be expected to be highly advantageous for diabetic patients with increased CV risk, while the diuretic effects of SGLT2 inhibitors may also be potentially effective in CHF patients who require frequent administration of diuretic agents. However, there is no evidence clinical evidence on the clinical safety of SGLT2 inhibitors for heart failure, and it is possible excess intravascular fluid depletion may be exacerbated following administration of SGLT2 in patients with heart failure taking diuretics. Given this current status, it is necessary to assess the safety and efficacy of SGLT2 inhibitors for diabetic patients with CHF.

The results of the EMPA-REG OUTCOME trial showed that administration of empagliflozin significantly reduced CV adverse outcomes in T2DM patients with higher CV risk [13]. Compared to the placebo group, any cause of death including worsening of heart failure, was significantly lower in the empagliflozin group. In addition, a 35 % relative risk reduction in hospitalization for heart failure was observed in the empagliflozin group. Although a significant reduction in hospitalization for heart failure was clearly documented, participants with heart failure comprised only about 10 % of the trial population at baseline. Moreover, about 40 % of the participants were taking diuretics at baseline, and therefore how to use SGLT2 inhibitors in conjunction with diuretics was of great concern in the clinical management of these patients. Taken together, the therapeutic effects of SGLT2 inhibitors in specific patients with heart failure have yet to be established (Fig. 1). It is therefore necessary to assess the clinical safety and efficacy of SGLT2 inhibitors focusing on T2DM patients with CHF.

Among the SGLT family, SGLT2 plays a central role in glucose reuptake specifically in the proximal renal tubule with high-capacity and low-affinity. SGLT1 is also a glucose transporter with low-capacity and high-affinity and is expressed mainly in the intestine, kidney, and heart. Compared with other SGLT2 inhibitors, canagliflozin has a relatively lower selectivity for SGLT2 over SGLT1 [51], and as a result also inhibits SGLT1 in the upper intestine, causing a delayed postprandial hyperglycemic response, similar to that seen with alpha-glucosidase inhibitors [52]. In addition, intestinal SGLT1 inhibition enhances glucagon-like peptide-1 secretion from L-cells in the lower intestine where residual glucose may reach [53]. Based on these results, simultaneous inhibition of SGLT1 by canagliflozin may also contribute, in part, to treatment of T2DM, despite its possible gastrointestinal side effects such as diarrhea caused by glucose-galactose malabsorption. However, the potential impacts of SGLT1 inhibition by canagliflozin on heart tissue still remain uncertain, due to the high blood protein-binding of canagliflozin of about 99 %. Cardiac SGLT1 is highly expressed in myocyte salcolemma and significantly up-regulated according to the pathological condition of cardiomyocytes with altered glucose requirements that occurs in diabetic or ischemic cardiomyopathy and in failing hearts [54]. Because the expression level of cardiac SGLT1 correlates with cardiac pathogenesis, inhibitors of the SGLT family may exert favorable effects on cardiac diseases [55]. On the other hand, studies in mouse models of ischemia–reperfusion injury have shown cardiac SGLT1 may have a cardioprotective role by optimizing glucose uptake into heart tissue [56]. Further in vitro and in vivo studies are needed to determine the clinical effects of canagliflozin on cardiac SGLT1 inhibition.

There are several limitations in the trial. First, the CANDLE trial is not a placebo-controlled trial. The aim of the trial is therefore to test the safety and non-inferiority of canagliflozin compared with glimepiride in T2DM patients with CHF. Second, as the trial is an open label design, there may be some bias towards the assessment of outcomes resulting from the physicians’ choice of treatment. However, there are strict definitions on the background treatment that will, in principle and if possible, remain unchanged during the trial interval. To overcome this possible bias, NT-proBNP, a primary endpoint, will be measured at a central laboratory, and all the data will be managed and statistically analyzed in a blinded manner. Finally, the trial interval of 24 weeks may be short to titrate the appropriate dose of glimepiride. According to a previous study from Japan that evaluated the safety and efficacy of glimepiride titration using self-monitoring blood glucose (SMBG) method [57], glimepiride treatment during 24 weeks resulted in a sufficient reduction in HbA1c level in the SMBG group and even in patients in the control group who were titrated empirically by their clinician without causing severe hypoglycemia. The average doses of glimepiride were 1.0 ± 0.8 mg/day in the SMBG group and 0.6 ± 0.3 mg/day in the control group, with no patient receiving glimepiride ≥3.5 mg/day. In addition, the HbA1c level at 24 weeks was significantly lower in patients receiving 0.5 mg/day compared with patients receiving >0.5 mg/day. This result indicates that glimepiride treatment for 24 weeks may not necessarily be too short to titrate glimepiride. Inappropriate titration of glimepiride may impact glycemic control and NT-proBNP levels in the glimepiride group, although there is currently insufficient evidence, as to whether or not, or the extent to which glimepiride treatment may affect NT-proBNP levels.

In summary, accumulated evidence suggests that SGLT2 inhibitors may have considerable impact on clinical diabetes care, with the potential to markedly improve clinical outcomes in patients with T2DM, especially those at higher risk of CV events. It is therefore important to evaluate the clinical implication of SGLT2 inhibitors in T2DM patients with CHF. The CANDLE trial is the first to test the safety and non-inferiority of canagliflozin for T2DM patients with CHF. This study has the potential to provide novel clinical insights on the treatment of diabetic patients with high CV risk.

